**Methods::**

The study is a single-blind, parallel-group, randomized controlled clinical trial consisting of a 4-to-6-week treatment period and a 6-month follow-up period. Included participants will be randomized into three groups and given a treatment regimen of acupuncture, qianliean suppository, respectively. Patients in each group will be treated for 1 month as a course of treatment. The clinical efficacy and changes in inflammatory factor levels in each group will be assessed at the end of treatment.

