## Introduction

1

Chronic prostatitis (CP) is the most common genitourinary disorder in adult men. Surveys have shown that 35% to 50% of men will be affected by prostatitis at some point in their lives.^[1]^ CP is a difficult class of disease to treat. The typical clinical presentation of the disease is prolonged and recurrent pain in the pelvic region. The duration of the painful discomfort is often greater than 3 months. Some patients also often have varying degrees of urinary symptoms and sexual dysfunction.^[2,3]^ CP is a complex and protracted disease, which is difficult to treat. It brings serious psychological and economic burdens to patients and seriously affects their quality of life. Some patients even develop severe anxiety and depression as a result, which in turn leads to many social problems. Currently, it has attracted the attention of clinicians in various countries. In recent years, Western medical treatment of CP has gradually changed from antibiotics to a combination of α-blockers, androgens, anti-anxiety and antidepressants, and the efficacy has improved, but patients are still not satisfied with the treatment effect.^[4]^ Therefore, it is often necessary to continuously increase the dose of medication in order to achieve a more satisfactory therapeutic effect. This may cause serious adverse effects and affect patient compliance with treatment. Based on the above status, more effective treatment modalities need to be further explored.^[5]^ As a traditional treatment modality inherited for thousands of years, acupuncture has been valued and widely used in the clinical treatment of CP in recent years.^[6]^ This treatment modality can improve the quality of life by promoting neuromuscular excitability and by enhancing the contractility of urethral muscles and perineal muscles. qianliean suppository is a topical preparation made from several Chinese herbs with the effects of clearing heat, relieving dampness, promoting laxity, resolving siltation, dispersing nodules, and relieving pain. This study will investigate the therapeutic effects of acupuncture combined with qianliean suppository on CP, aiming to provide valuable evidence-based medical evidence for clinicians.

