#### Primary outcome measure

2.5.1

The CP symptom index (NIH-CPSI) with prostatitis-related sexual function index score will be performed before and after treatment. The changes of urodynamic indexes will be observed in each group before and after treatment, and the specific indexes included maximum urinary flow rate, maximum bladder capacity, maximum forced urinary muscle pressure and bladder stability. The observation times for the primary outcome indicators are shown in Table 1.

**Table 1 T1:** Treatment schedule and outcome measures.

Items	Before Treatment	Treatment period, twice a week, 8 times in total (treatment starts within 1 wk after registration)				Post observation Period
TIME POINT	Registration	wk 1	wk 2	wk 3	wk 4	1 wk later Treatment completion
Inclusion criteria	√					
Exclusion criteria	√					
Informed consent	√	√	√	√	√	√
Confirmation of subjective symptoms	√		√		√	√
Chronic prostatitis symptom index	√	√	√	√	√	√
prostatitis-related sexual function index Observation of adverse events	√		√		√	

Clinical efficacy evaluation criteria: significant effect: the symptoms of urinary disorder disappeared after treatment, no pain and discomfort, and normal sexual function will be restored at the same time; effective: the symptoms of urinary disorder basically disappeared, a little pain and discomfort existed, pain will be tolerated, and sexual function will be basically restored to normal; ineffective: the situation of urinary disorder did not improve, obvious pain and discomfort existed, and no significant change in sexual function will be seen. The total effective rate =  (the number of effective cases to the number of effective cases)/total cases × 100%.

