### Statistical analyses

2.7

The case information collected by Excel will be imported into SPSS 25.0 statistical software to establish the analysis database and complete the statistical analysis of the data. Normality test will be performed by Kolmogorov-Smirnov method; chi-square test will be performed by Levene method. The measurement data conform to normal distribution and will be described by means and standard deviations, and comparisons between groups will be made by one-way ANOVA ANOVA or independent samples *t*-test; two-way comparisons will be made by Bonferroni method corrected *P*-value; not conforming to normal distribution, the measurement data will be described by medians and quartiles, and comparisons between groups will be made by Kruskal-Wallis method test or The Mann-Whitney *U* test will be used for comparison between groups, and the Dunnett's method will be used for comparison between two groups. The dichotomous data will be expressed as composition ratio and frequency in describing the distribution pattern, and the chi-square test and exact Fisher test will be used for comparison between groups. NIH-CPSI scores, mean urine flow rate and maximum urine flow rate will be compared between the two groups of patients at different time points using repeated measures ANOVA-generalized linear model equations.

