For the treatment of this disease, the common treatment options can be divided into pharmacotherapy (α-blockers, antibiotics, analgesics and botanicals), physiotherapy (biofeedback, microwave therapy, acupuncture) and surgery. Several randomized controlled trials and Meta-analyses have shown acupuncture to be effective in CP^[11–13]^ and a relatively safe treatment. Studies have shown that acupuncture can improve patients’ symptoms, reduce patients’ NIH-CPSI scores and decrease the number of white blood cells.^[14]^ However, there is still a lack of systematic and comprehensive clinical studies on acupuncture for the treatment of this disease, and most trials lack follow-up to understand the long-term efficacy. Therefore, this study will objectively evaluate the short-term and long-term clinical efficacy of different treatment regimens and the effect on the level of inflammatory factors in the organism by designing a standardized clinical trial with an acupuncture group and a Qianliean suppository group with NIH-CPSI scale score as the main outcome index, combined with a long follow-up. This study hopes to provide more ideas for the clinical treatment of CP.

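### The total effective rate formula names 'effective' twice and omits 'significant effect', and the three response grades leave partial responders without a grade

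*Protocol article*

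**What the plan says.** Section 2.5.1 (Primary outcome measure) lists NIH-CPSI, a sexual function index and urodynamic measures, and then sets out clinical efficacy criteria in three grades:

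- Top grade: "significant effect: the symptoms of urinary disorder disappeared after treatment, no pain and discomfort, and normal sexual function will be restored at the same time".
- Middle grade: "effective: the symptoms of urinary disorder basically disappeared, a little pain and discomfort existed, pain will be tolerated, and sexual function will be basically restored", that is, near-normal function.
- Bottom grade: "ineffective: the situation of urinary disorder did not improve, obvious pain and discomfort existed, and no significant change in sexual function will be seen".

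From these grades the article prints the total effective rate as "the number of effective cases to the number of effective cases)/total cases", times 100%. The abstract says of timing: "The clinical efficacy and changes in inflammatory factor levels in each group will be assessed at the end of treatment". For dichotomous data, section 2.7 says that "the chi-square test and exact Fisher test will be used for comparison between groups"; it does not name this rate. The Discussion describes the trial as one "with NIH-CPSI scale score as the main outcome index". Nothing elsewhere in the article restates the formula or says where a patient who fits none of the grades should go.

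**The concern.** There are two separate defects, and correcting one does not correct the other.

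**Numerator.** A total effective rate built on these grades should count both favourable ones. The printed expression uses one of them, twice. Followed literally, a patient who moves from effective to significant effect lowers the rate of his arm.

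**Grades.** Each grade is defined by conditions on urinary symptoms, pain and sexual function taken together. The middle grade needs near-complete resolution and the bottom grade needs essentially no change. Everything between is undefined, as is any mixed pattern across domains. In a chronic pain condition, partial response is a plausible result. Whoever grades such a patient has to invent a rule, and the rate then depends on that rule as well as on the treatment.

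**Working it through.** The article states no rate, count or sample size for this endpoint, so there is no figure to reproduce. All counts below are assumptions, chosen to show what the printed rule can do.

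Notation, per arm of N = 100: S = significant effect, E = effective, I = ineffective, P = improved but fitting no grade.

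**1. The printed numerator (P = 0)**

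Arm A: S = 50, E = 30, I = 20. Arm B: S = 10, E = 40, I = 50.

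| Reading | Formula | Arm A | Arm B | Better arm |
|---|---|---|---|---|
| Conventional | (S + E)/N | (50 + 30)/100 = 80% | (10 + 40)/100 = 50% | A |
| Printed, as a sum | (E + E)/N | 60/100 = 60% | 80/100 = 80% | B |
| Printed, effective counted once | E/N | 30/100 = 30% | 40/100 = 40% | B |
| Printed, as a literal ratio | (E/E)/N | 1/100 = 1% | 1/100 = 1% | none |

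The order reverses whenever the arm with fewer E cases has an excess of S cases larger than its shortfall in E. Here A has 10 fewer E and 40 more S. A second set gives the same pattern: S/E/I of 50/20/30 against 20/40/40 yields 70% v 60% conventionally, 40% v 80% as a sum, and 20% v 40% with effective alone.

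The sum reading also exceeds 100% once more than half of an arm is graded effective: E = 60 gives 120/100 = 120%. Such a count cannot be split into responders and non-responders for a chi-square or Fisher test. The literal ratio does not depend on outcome at all.

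**2. The gap between grades (numerator already corrected to S + E)**

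Arm A: S = 20, E = 30, P = 40, I = 10. Arm B: S = 25, E = 30, P = 10, I = 35.

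| Handling of P | Arm A | Arm B | Better arm |
|---|---|---|---|
| Counted as failure | 50/100 = 50% | 55/100 = 55% | B |
| Counted as effective | 90/100 = 90% | 65/100 = 65% | A |
| Dropped from the denominator | 50/60 = 83.3% | 55/90 = 61.1% | A |

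The order again depends on a rule that the article does not give. Within one arm, the rate moves by the full share of P between the first two rows: 40 points in A and 10 in B.

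**3. Which patients fit no grade**

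- Symptoms clearly reduced in every domain but still moderate: not near resolution, so not effective; improved, so not ineffective.
- Pain resolved but urinary symptoms unchanged, or the converse: each of the three definitions fails on one domain.
- Pain fully gone with slight residual urinary symptoms: short of the top grade, while the middle grade, read literally, requires some remaining pain.
- Sexual function normal at entry: there is nothing to restore. The Introduction says "Some patients also often have varying degrees of urinary symptoms and sexual dysfunction", and sexual dysfunction is in neither the diagnostic criteria (section 2.2.1) nor the eligibility criteria (section 2.2.2), so such men can be enrolled.

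**The case against.** The strongest reply is that the formula is an obvious slip. Three grades have just been named, two identical terms are joined by a word where a plus sign would be expected, and the result is called a total. An analyst would very likely compute (S + E)/N, so the first reversal describes an analysis that may never be run. That is fair, and it makes the numerator easy to correct. It does not make the printed rule right, and it leaves the gap between grades untouched.

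It can also be said that a condensed article may leave the grading of borderline cases to the full protocol or the case observation form. But the article does state the grades, and as stated they do not cover the patients.

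Four stronger inferences are tempting, and the article does not support them:

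- *That the trial's main result is at risk.* The rate stands under the primary heading, but the Discussion names NIH-CPSI as the main index, Table 1 has no row for the grade, and the repeated-measures analysis in section 2.7 does not include it.
- *That unmasked raters will do the grading.* The trial is described as single-blind, and section 2.3 does not say who is blinded. Masking of the assessor is neither stated nor excluded.
- *That the urinary criterion also fails for many patients at baseline.* The diagnosis requires the symptom criterion in section 2.2.1, and on a natural reading this includes lower urinary tract symptoms. The baseline problem is clear only for sexual function.
- *That the denominator must be all randomised patients with missing counted as ineffective.* Section 2.6 already defines a full analysis set (randomised and treated at least once, last observation carried forward). A different denominator would conflict with it and is not needed to correct this error.

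**Conclusion.** Both defects stand. The numerator is wrong on every reading of the printed words: it leaves out the best responders, and it yields a rate that can exceed 100%, a rate that counts the top grade as failure, or a constant. The grades are not exhaustive, and this remains after the numerator is corrected.

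On size, the illustrations turn 80% v 50% into 60% v 80% (or 30% v 40%) for the formula, and 50% v 55% into 90% v 65% for the gap. They rest wholly on assumed counts and show that reversal can happen, not that it will. The consequence is confined to the total effective rate, one of several measures under the primary heading. It is worth correcting before recruitment, because a grading rule settled after outcomes are known would be open to challenge.

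**What to change.** In section 2.5.1:

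1. Print the formula as total effective rate = (significant effect + effective cases)/total cases in the arm × 100%, and state that total cases means the analysis set defined in section 2.6.
2. Define ineffective as every graded patient who does not reach at least the effective grade. Word the effective grade as an upper limit (at most slight residual symptoms), so that a patient without pain is not excluded from it.
3. State that a domain normal at baseline counts as met if it is still normal at assessment.

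The cost is a change of wording; no new data are needed. The downside is that partial responders now count as ineffective, so the reported rate may be lower than under lenient case-by-case grading.

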#### Secondary outcome measures

2.5.2

Four ml of fasting elbow venous blood will be collected from the participants before and after treatment, and the blood will be shaken in a tube with anticoagulant, centrifuged at 3000 r/min for 10 min and tested immediately. Serum inflammatory factors, including interleukin (IL)-1β, IL-6 and tumor necrosis factor-a (TNF-a), will be measured by enzyme-linked immunosorbent assay in each group of patients.

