### Study design and setting

2.1

The study is a single-blind, parallel-group, randomized controlled clinical trial consisting of a 4- to 6-week intervention and a 6-month follow-up period. The study will be conducted at one site, the Affiliated Hospital of Shaanxi University of Chinese Medicine. A brief flow chart of the entire study is shown in Figure 1. This study will adopt a parallel controlled design approach. We will ensure a balance of baseline data across groups by having an adequate sample size and a completely randomized grouping method. The study will be approved by the Ethics Committee of the Affiliated Hospital of Shaanxi University of Chinese Medicine. We will not begin recruiting participants until ethics committee approval has been obtained.

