### Interventions

2.4

(1)Acupuncture group: selected acupoints: *Shensu, Zhongliao, Huiyang, and Sanyinjiao* (all taken bilaterally). The acupuncture points will be positioned with reference to the 2006 National Standard of the People's Republic of China (GB/T 12346–2006) “Name and Positioning of Acupuncture Points”. After local sterilization of the acupoints, Shensu and Sanyinjiao will be needled with 0.3 × 40 mm milli-needles at a depth of 20 to 30 mm; Zhongliao and Huiyang will be needled with 0.3 × 75 mm milli-needles at a depth of 50 to 70 mm; the needles will be retained for 30 minutes.(2)Qianliean suppository group: use prostate suppository (National Drug Administration Z10980066, specification 2g × 5 s) for treatment. This product is brown or black-brown torpedo type suppository. Usage: The drug is inserted into the anus at night before bedtime, placed at a depth of 2 cm, 1 capsule each time, once a day. The ingredients of this drug are: extracts of Chinese herbs such as *Huangbai, Huzhang, Zhizi, Dahuang, Zelan, Maodongqing, Wuzhuyu, Weilingxian, Shichangpu and Lizihe*. Precautions for use: After the suppository is inserted into the anus, if there are uncomfortable symptoms such as bowel movement, abdominal pain and diarrhea, the method of use can be improved, such as applying vegetable oil outside the suppository or placing the suppository deeper, after the rectum adapts, the above symptoms can be reduced or disappear.(3)Combination therapy group: The treatment methods of (1) and (2) are combined.

Patients in each of the above groups will be treated for 1 month as a course of treatment. Patients in each group will be asked to abstain from sexual intercourse during the treatment period, to ensure the cleanliness of the perineal area, to observe the adverse reactions and to provide timely and effective treatment to ensure the treatment effect.

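### The cytokine outcome is called serum but the described tube yields plasma, and immediate testing read literally puts each patient's before and after samples in different ELISA runs

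*Protocol article*

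**What the plan says.** Section 2.5.2 (Secondary outcome measures) sets the sampling times: "Four ml of fasting elbow venous blood will be collected from the participants before and after treatment". On handling, it says that "the blood will be shaken in a tube with anticoagulant, centrifuged at 3000 r/min for 10 min and tested immediately". The outcome itself is then stated: "Serum inflammatory factors, including interleukin (IL)-1β, IL-6 and tumor necrosis factor-a (TNF-a), will be measured by enzyme-linked immunosorbent assay". These three cytokines are the only outcomes listed in that section.

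The Methods part of the abstract makes change the quantity of interest: "The clinical efficacy and changes in inflammatory factor levels in each group will be assessed at the end of treatment".

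The time between the two samples follows from the treatment period. Section 2.4 (Interventions) says: "Patients in each of the above groups will be treated for 1 month as a course of treatment". Section 2.1 (Study design and setting) describes a trial "consisting of a 4- to 6-week intervention and a 6-month follow-up period". Table 1 shows eight sessions over four weeks.

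For normally distributed continuous data, section 2.7 (Statistical analyses) says that "comparisons between groups will be made by one-way ANOVA ANOVA or independent samples" *t*-test, with rank tests otherwise. It does not say whether the cytokine comparison uses change scores or post-treatment values.

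**The concern.** There are two separate problems in the same two sentences.

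**Specimen.** An anticoagulant prevents clotting, so centrifuging that blood gives plasma. Serum needs a tube in which the blood clots. Laboratory staff who follow the text will report plasma under the name serum, or they will change the tube and depart from the written procedure. If different staff resolve this differently over time, a patient's pair could even mix the two.

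**Timing of the assay.** If each sample is tested as soon as it is spun, the before sample is assayed about a month before the after sample, in another run with its own standard curve. The difference between the two readings then carries the error of two runs. On a shared plate this error would largely drop out. What is at stake is precision for IL-1β, IL-6 and TNF-α and, for the change within each group, the ability to separate a treatment effect from assay drift.

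**Working it through.** **Step 1: the specimen.** Set the two sentences of section 2.5.2 side by side. The procedure is an anticoagulant tube followed by centrifugation, which gives plasma. The outcome name is serum. The procedure cannot produce the named specimen. This step needs no assumption.

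**Step 2: can the two samples share a run?** Samples are taken before and after treatment, and treatment lasts one month (section 2.4) or four to six weeks (section 2.1). With immediate testing taken literally, the two assays are about a month apart and cannot share a run.

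**Step 3: size of the effect on a change score.** The document states no figure to reproduce: it gives no assay CV, cytokine SD, sample size or effect size. All inputs below are assumptions, on the log scale:

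- s, SD of the true within-patient change: 0.2, 0.3, 0.5
- w, intra-assay CV: 0.06
- r, inter-assay CV: 0.05 to 0.20

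Formulas:

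- Same plate: Var = s² + 2w²
- Different runs: Var = s² + 2w² + 2r²
- Ratio = 1 + 2r² / (s² + 2w²)

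With 2w² = 0.0072, the denominators are 0.0472, 0.0972 and 0.2572 for s = 0.2, 0.3 and 0.5. The numerators 2r² are 0.005, 0.020, 0.045 and 0.080.

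| s | r = 0.05 | r = 0.10 | r = 0.15 | r = 0.20 |
|---|---|---|---|---|
| 0.2 | 1.11 | 1.42 | 1.95 | 2.69 |
| 0.3 | 1.05 | 1.21 | 1.46 | 1.82 |
| 0.5 | 1.02 | 1.08 | 1.17 | 1.31 |

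The range is about 1.02 to 2.7.

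**Step 4: cross-check with other inputs.** Write s² = 2b², where b is the within-person biological SD. Take b from 0.15 to 0.50, w from 0.05 to 0.10 and r from 0.05 to 0.20, again all assumed. The ratio then runs from 1.01 to 2.6. A middle case (b = 0.30, w = 0.10, r = 0.15) gives (0.09 + 0.01 + 0.0225) / (0.09 + 0.01) = 1.225. For illustration, take a two-sided 5% test, 80% power and a true difference of 0.5 SD of the same-run change. The need per arm rises from 63 to 77, or power at 63 per arm falls from 0.80 to 0.72.

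**Step 5: if post-treatment values are compared.** Run error then enters once, against the spread between persons. With an assumed between-person log SD of 0.6 and w = 0.06, the ratio is 1 + r² / (0.36 + 0.0036). This is 1 + 0.0025/0.3636 = 1.01 at r = 0.05, 1.03 at r = 0.10 and 1.11 at r = 0.20.

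**Step 6: between arms and within arms.** Patients from different arms who share a run share its error. In the extreme, with all before samples in one run and all after samples in another, the run term cancels from the difference between arms. The ratios in Steps 3 and 4 are therefore upper bounds for between-arm contrasts. Within one arm nothing cancels in this way. The after sample is always the later one, so a steady drift of kit or calibration adds to every patient's change in the same direction, and a larger sample does not remove it.

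**The case against.** The strongest case against the point runs as follows.

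- *The wrong specimen name does not bias the comparison of arms.* This is correct, because one procedure is described for all patients. The consequence is mislabelled results, but the contradiction still has to be removed.
- *Testing may loosely mean processing.* If so, the run argument weakens. The text does say tested, however, and under the looser reading the wording would still need correction.
- *Plate layout, controls and run schedules belong in a laboratory manual.* This is accepted. That the article mentions no bridging controls and no adjustment for run is not a finding. The point rests on the rule that the article does state.
- *The size is unknown.* This stands. A reader might take a middle value of s = 0.3 with inter-assay CVs of 10 to 20%, obtain ratios of 1.21 to 1.82, and conclude that the plan loses 17% to 45% of its patients for this outcome (1 − 1/ratio). The documents do not support that. Over the whole range in Step 3 the same conversion gives about 2% to 63%, and even those values are upper bounds between arms.
- *Arms may share runs.* A reader might infer that, because patients enter one by one, few from different arms fall in the same run, so that the error does not cancel. The article gives no recruitment rate, sample size or plate schedule, so this cannot be said.

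The cytokines are also secondary: the Discussion names the NIH-CPSI score as the main outcome. This limits the weight of the point.

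**Conclusion.** The specimen contradiction is established from the text alone and needs correction. The assay-timing point holds in direction, given a literal reading of immediate testing and change as the quantity of interest. Separate runs add 2r² to the variance of each within-patient change, and drift can be mixed with time in within-group changes. Between randomised arms the effect is mainly lost precision. A reader might infer bias between arms, but with the same handling in every arm the documents give no ground for it.

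The size cannot be taken from the documents. Under the assumed values it ranges from negligible (variance ratio 1.02) to large (2.7) for change scores. It is lower for between-arm contrasts where arms share runs, and about 1.01 to 1.11 in the illustration with post-treatment values. The point is worth acting on because the correction is cheap and is best made before the first sample is assayed.

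**What to change.** 1. Name one specimen type throughout section 2.5.2: either keep serum and specify a tube without anticoagulant, or keep the tube and write plasma.
2. Replace immediate testing with wording such as: samples are centrifuged promptly, aliquoted and frozen; each patient's before and after samples are assayed on the same plate, with arms mixed across plates.

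The cost is freezer storage, one freeze-thaw cycle applied equally to all samples, and later results. If immediate testing has to stay for practical reasons, bridging controls across runs and an adjustment for run in the analysis are the fallback.
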